### **5.3 Study procedures**

Cohort A: children will undergo venepuncture in the presence of a parent during the acute phase of measles, to collect one tube of approximately 9 ml heparinised blood. In addition, a throat swab and a nose swab will be collected in virus transport medium. In Cohort B children will undergo venepuncture at two time points, but no other clinical specimens will be collected. These children are in normal health at the moment of sample collection. The blood sampling can be considered as a negligible risk procedure. The procedure will be performed by a skilled person. In addition, all children will be offered EMLA as a local anaesthetic to reduce pain during the venepuncture. Obtaining a throat- and nose swab can be inconvenient for children and the nose swab may cause a minor nose bleed.

### **5.4 Withdrawal of individual subjects**

Subjects can leave the study at any time for any reason if they wish to do so without any consequences. The investigator can decide to withdraw a subject from the study for urgent medical reasons. Minors cannot be forced to undergo interventions against his or her will. This study will be conducted according to the Code of Conduct applicable to minors as written by the Paediatric Association of the Netherlands (Nederlandse Vereniging voor Kindergeneeskunde). The parents will be informed about the possibility to withdraw their children at any moment in the study without consequences for the medical care in an information letter they will receive upon inclusion.

#### **5.4.1 Specific criteria for withdrawal (if applicable)**

Not applicable.

### **5.5 Replacement of individual subjects after withdrawal**

If parents have consented but children refuse to cooperate before any samples have been collected, the subject will be replaced. If samples have already been collected the subject will remain included.

### **5.6 Follow-up of subjects withdrawn from treatment**

Not applicable.

### **5.7 Premature termination of the study**

Not applicable.

## SAFETY REPORTING

### 5.8 Section 10 WMO event

In accordance to section 10, subsection 1, of the WMO, the investigator will inform the subjects and the reviewing accredited METC if anything occurs, on the basis of which it appears that the disadvantages of participation may be significantly greater than was foreseen in the research proposal. The study will be suspended pending further review by the accredited METC, except insofar as suspension would jeopardise the subjects' health. The investigator will take care that all subjects are kept informed.

### 5.9 AEs, SAEs and SUSARs

#### 5.9.1 Adverse events (AEs)

Adverse events are defined as any undesirable experience occurring to a subject during the study, whether or not considered related to [the investigational product / the experimental intervention]. All adverse events reported spontaneously by the subject or observed by the investigator or his staff will be recorded.

#### 5.9.2 Serious adverse events (SAEs)

A serious adverse event is any untoward medical occurrence or effect that at any dose:

- results in death;
- is life threatening (at the time of the event);
- requires hospitalisation or prolongation of existing inpatients' hospitalisation;
- results in persistent or significant disability or incapacity;
- is a congenital anomaly or birth defect;
- Any other important medical event that may not result in death, be life threatening, or require hospitalization, may be considered a serious adverse experience when, based upon appropriate medical judgement, the event may jeopardize the subject or may require an intervention to prevent one of the outcomes listed above.

The principal investigator will report the SAEs through the web portal *ToetsingOnline* to the accredited METC that approved the protocol, within 15 days after the principal investigator has first knowledge of the serious adverse reactions.

SAEs that result in death or are life threatening should be reported expedited. The expedited reporting will occur not later than 7 days after the responsible investigator

has first knowledge of the adverse reaction. This is for a preliminary report with another 8 days for completion of the report.

### **5.9.3 Suspected unexpected serious adverse reactions (SUSARs)**

Not applicable.

### **5.10 Annual safety report**

Not applicable.

### **5.11 Follow-up of adverse events**

All AEs will be followed until they have abated, or until a stable situation has been reached. Depending on the event, follow up may require additional tests or medical procedures as indicated, and/or referral to the general physician or a medical specialist. SAEs need to be reported till end of study within the Netherlands, as defined in the protocol.

### **5.12 [Data Safety Monitoring Board (DSMB) / Safety Committee]**

Not applicable

## 6. STATISTICAL ANALYSIS

In cohort A the outcomes will be presented as qualitative data: the percentage MV-infected cells within different white blood cell populations and subpopulations will be determined by flow cytometry. These data will be linked to the time point of sample collection, expressed as the number of days before or after onset of rash. To test our hypothesis that MV predominantly infects memory lymphocytes, the percentages MV-infected cells within the memory B-lymphocyte, memory CD4+ T-lymphocyte and memory CD8+ T-lymphocyte subpopulations will be compared with those in the naïve B-lymphocyte, CD4+ T-lymphocyte and CD8+ T-lymphocyte subpopulations, respectively. For this comparison we will use a paired t-test on log-transformed data. If the data are not normally distributed, a non-parametric test will be used for this comparison (Mann-Whitney U-test).

In cohort B the data will be presented as precursor frequencies of memory lymphocytes to infections unrelated to measles. The difference between these precursor frequencies before and after measles will be analysed by using a paired t-test on log-transformed data. If the data are not normally distributed, a non-parametric test will be used for this comparison (Mann-Whitney U-test). Patients or data will only be included if memory lymphocyte populations can be identified in the pre-exposure PBMC sample.

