**Cohort B** consists of unvaccinated children aged 6-13 years. These children will be recruited by contacting orthodox protestant schools with low vaccination coverage. Via the schools (groups 3-8) we will approach families that have not yet been exposed to MV, but live in an area that is expected to become part of the measles outbreak. One tube (maximum volume 9 ml) of heparinised blood will be collected; PBMC will be isolated and frozen. The parents will be contacted every two weeks by email or telephone, to monitor whether the children have contracted measles. Two to three weeks after the end of the measles outbreak in the school, a second 9 ml heparinised blood sample will be collected from the same children. This second blood sample will also be collected if the child did not experience measles during this outbreak. In this case the child will serve as an internal control: according to our hypothesis the frequency of pre-existing memory lymphocytes should remain stable in children that do not develop measles. However, we estimate the chances of unprotected children escaping from measles virus infection at a school with low vaccination coverage as minimal. The main

study parameter in this group will be the quantification of pre-existing memory lymphocyte populations in peripheral blood by tetramer staining, to test the hypothesis that these populations are decimated during measles.

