### **1.4 Sample size calculation**

#### **Cohort A:**

To obtain significant percentages and proof of lymphocyte memory subset infection by MV, we anticipate that we need PBMC samples of at least 25 children who are in the incubation phase of measles and have detectable levels of infected cells in their PBMC. Using multi-color flow cytometry we will identify the phenotype of the infected cells. However, there are uncertain variables that need to be taken into account.

The clinical specimens that are required to meet our study objective need to be collected during the incubation phase of the disease, when neither clinical nor laboratory diagnosis of measles is possible at the bedside. Therefore, it is a possibility that children that prove not to be MV-infected are included in this cohort. Furthermore, MV infection causes lymphopenia. As a result, isolation of PBMC from blood may in some cases not result in

sufficient numbers of cells for the flow cytometric staining to characterize the MV-infected subsets.

It is difficult to estimate how many samples will be lost due to one of these two causes. However, since both the laboratory diagnosis and the quality and quantity of PBMC are available within two days after collection of clinical specimens, we will be able to monitor the build-up of data in this cohort in real time. As soon as we have the required 25 successful PBMC stains of laboratory-confirmed measles cases, we will stop recruiting children to this cohort. In total, we will not include more than 100 children in this cohort.

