**Cohort B:**

To obtain significant data in cohort B, we require paired pre- and post-measles PBMC of at least 50 children. This will allow statistical comparison of the precursor frequencies of circulating memory lymphocyte populations before and after measles.

Here, we need to take other uncertainties into account. Most importantly, it is a possibility that children that consent to collection of a pre-measles blood sample may decide to withdraw their consent for collection of a second sample. Historically, it has been observed that this occurs in approximately 50% of the children. An additional theoretical risk is that the school of the children does not become involved in the measles outbreak. However, observations from previous measles outbreaks in the bible belt suggest that this risk is low, especially since we intend to recruit children at schools with very low vaccination coverage. Finally, the detection of memory lymphocyte populations by flow cytometry will determine on the availability of suitable tetramers that can be used to stain these populations by flow cytometry. Tetramers are restricted to specific HLA-haplotypes, and thus technical limitations may result in the inability to detect memory lymphocytes in a specific patient.

As a result, we estimate that it will be necessary to collect a first blood sample of 100 children.

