## 6.2 Secondary study parameter(s)

**Cohort A:** secondary study parameters in cohort A are the identification and characterization of cell-free and cell-associated virus, both in terms of quantity (what virus concentrations are present in the upper respiratory tract in relation to transmissibility of MV) and quality (what does transmissible MV look like under the electron microscope?). In addition, we will investigate what cytokines, chemokines and acute phase proteins can be measured in the plasma during the early stage of acute MV infection, in relation to the level of lymphopenia (reduced lymphocyte numbers in peripheral blood). These data will be described qualitatively, and do not require statistical analysis.

**Cohort B:** secondary parameters in cohort B are the measurement and characterization of MV-specific humoral and cellular immune responses. Massive expansion of MV-specific (and bystander) B- and T-lymphocyte populations is an essential characteristic of our immune suppression model; we will explore different methods to demonstrate that the qualitative composition of the circulating lymphocyte pool of children after measles is dramatically altered as compared to the pre-infection sample. If successful, these data will be analysed using a similar approach as above: by paired t-test on log-transformed data or by Mann-Whitney U-test if data are not normally distributed.

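### The non-parametric fallback for the paired, within-child comparisons is the Mann-Whitney U-test, which is for independent groups: it discards the pairing, is conservative, and loses power as the within-child correlation rises

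*Protocol*

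**What the plan says.** Section 6 defines two primary comparisons.

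- **Cohort A.** The percentage of infected cells in each memory subset (B, CD4+ T, CD8+ T) is compared with that in the matching naive subset. The first-choice test is paired: "For this comparison we will use a paired t-test on log-transformed data".
- **Cohort B.** "The difference between these precursor frequencies before and after measles will be analysed by using a paired t-test on log-transformed data".

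Each is followed by the same fallback: "If the data are not normally distributed, a non-parametric test will be used for this comparison (Mann-Whitney U-test". Section 6.1 refers the primary parameters of both cohorts back to this text. Section 6.2 applies the same rule to the cohort B secondary parameters: "by paired t-test on log-transformed data or by Mann-Whitney U-test if data are not normally distributed".

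The design makes both data sets paired. In cohort A each child gives a single blood tube, so memory and naive percentages come from the same sample. In cohort B, under Study Design, "a second 9 ml heparinised blood sample will be collected from the same children", and section 1.4 sets its target in pairs: "we require paired pre- and post-measles PBMC of at least 50 children". No paired rank test is named anywhere in the protocol.

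**The concern.** The Mann-Whitney U-test compares two unrelated groups. It is not the rank-based counterpart of the paired t-test. Used here, it pools the two columns, ranks them together and ignores which values belong to the same child. Differences between children then count as noise, although the paired design exists to remove them.

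The fallback cannot be read as a between-group contrast, such as children who had measles against children who escaped it. Each time, section 6 ties it to the comparison just defined, which is within-child.

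At stake is a missed finding. If normality is rejected, a real but moderate depletion (cohort B) or infection preference (cohort A) could be reported as non-significant, in a study that takes blood from children who gain no benefit from it.

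**Working it through.** **The plan's own figure.** Section 1.4 expects about half of the cohort B children to withdraw before the second sample ("Historically, it has been observed that this occurs in approximately 50% of the children"). 50 / (1 − 0.5) = 100 first samples, which matches the protocol. This confirms that 50 counts pairs. It does not bear on the choice of test. The targets of 25 children and 50 pairs cannot be re-derived, because no alpha, power, effect size or SD is stated.

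**Inputs.** From the protocol: n = 25 (cohort A) and n = 50 pairs (cohort B). Assumed, because the protocol gives none: normal log10 values, SD 0.5 log10 at each measurement, two-sided alpha 5%, within-child correlation ρ from 0 to 0.8, and shifts of 0.15, 0.3 and 0.5 log10. These shifts are falls of 1 − 10^−0.15 = 29%, 1 − 10^−0.3 = 50% and 1 − 10^−0.5 = 68%.

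**Why the test is conservative.** The variance of the mean within-child difference is 2σ²(1 − ρ)/n. An independent-groups test in effect uses 2σ²/n. Its statistic is therefore too small by a factor of about √(1 − ρ), and its null rejection rate is roughly 2Φ(−1.96/√(1 − ρ)):

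- ρ = 0.3: 1.96/0.837 = 2.34, giving 1.9%
- ρ = 0.5: 1.96/0.707 = 2.77, giving 0.6%
- ρ = 0.8: 1.96/0.447 = 4.38, giving less than 0.01%

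Simulation of the Mann-Whitney test itself (20,000 replicates per setting, n = 25 and 50) gives 2.2%, 0.8% and 0.01%. At ρ = 0 it gives 5.0%. The signed-rank test stays at 4.7% to 5.2% throughout.

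**Power, Mann-Whitney against signed-rank** (same simulation; simulation error at most about 0.7 percentage points):

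| Shift (log10) | n | ρ = 0 | ρ = 0.3 | ρ = 0.5 | ρ = 0.8 |
|---|---|---|---|---|---|
| 0.15 | 50 | 30% / 30% | 27% / 40% | 25% / 53% | 16% / 90% |
| 0.15 | 25 | 17% / 17% | 13% / 22% | 10% / 28% | 4% / 59% |
| 0.3 | 50 | 82% / 82% | 86% / 93% | 90% / 98% | 98% / 100% |
| 0.3 | 25 | 52% / 50% | 53% / 66% | 54% / 80% | 58% / 99% |
| 0.5 | 50 | 100% / 100% | 100% / 100% | 100% / 100% | 100% / 100% |
| 0.5 | 25 | 92% / 91% | 95% / 98% | 97% / 100% | 100% / 100% |

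With heavier tails (t with 3 degrees of freedom) the pattern is the same but milder. At 50 pairs, with the shift set to about 80% nominal paired-t power, Mann-Whitney against signed-rank gives 96% against 92% at ρ = 0, 75% against 92% at 0.5 and 26% against 92% at 0.8.

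**The case against.** The strongest reply concerns size and reach.

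- **A reader might infer that most of the power is lost.** The documents do not support that. They give no correlation or effect size. The loss is nil at correlation 0 and small for large effects, and the protocol's hypothesis is a very large depletion: at a 68% fall both tests exceed 90%. For normal data with a shift giving the paired t-test about 80% power, the loss passes one half only from a correlation of about 0.6 upward. This reply stands and limits the claim.
- **The error creates no false positives** when the correlation is positive. This stands. The harm is a missed effect.
- **A reader might infer that the fallback will become the operative primary analysis**, because rare-cell percentages can be zero and a zero has no logarithm. No figure shows how likely that is. Cohort A needs detectable infected cells, and cohort B needs memory populations found in the first sample. Zeros in naive subsets or second samples remain possible, but the inference is speculation.
- **A reader might also infer that the trigger is wrong**, because normality should be judged on the differences. The wording is ambiguous: in cohort B it directly follows a sentence about the before-after difference. How normality is judged is a detail that a statistical analysis plan may settle.

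None of this rescues the named test. The protocol does not leave the fallback open. It names a test for the wrong design.

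**Conclusion.** Wrong as written, in three places: cohorts A and B in section 6, and the cohort B secondary parameters in section 6.2. Naming an independent-groups test for a paired comparison is an error whatever the correlation. Its cost, if the fallback is used, depends on quantities that the protocol does not state. At 50 pairs and a 29% fall it runs from nothing at correlation 0 to a drop from 90% to 16% at correlation 0.8. At 25 children and a 50% fall it is 80% to 54% at correlation 0.5, and 99% to 58% at 0.8. It is slight for a fall of about two thirds or more. These figures rest on normal log10 data, SD 0.5 log10 and two-sided 5%, and the conservative direction rests on a positive within-child correlation. The first-choice paired t-test on log-transformed data is sound and is not in question.

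**What to change.** In all three places, replace the Mann-Whitney U-test by the Wilcoxon signed-rank test on the within-child differences, taken on the log scale where it is defined. Keep the paired t-test on log-transformed data as the first choice; making the signed-rank test primary outright would be a preference, not a correction.

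The cost is a wording change in three sentences, made before analysis. It needs no further children, samples or measurements.

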### 6.1 Primary study parameter(s)

**Cohort A:** the main study parameter of this cohort is the phenotypic characterization of MV-infected white blood cells by multicolour flow cytometry. Our hypothesis is that these will be predominantly memory lymphocytes. These data will be analysed as described above.

**Cohort B:** the main study parameters in this cohort are the identification of pre-existing memory lymphocyte populations in peripheral blood before MV infection (by tetramer staining in combination with multicolour flow cytometry) and the change in the frequency of these populations following MV infection. These data will be analysed as described above.

## 6.2 Secondary study parameter(s)

**Cohort A:** secondary study parameters in cohort A are the identification and characterization of cell-free and cell-associated virus, both in terms of quantity (what virus concentrations are present in the upper respiratory tract in relation to transmissibility of MV) and quality (what does transmissible MV look like under the electron microscope?). In addition, we will investigate what cytokines, chemokines and acute phase proteins can be measured in the plasma during the early stage of acute MV infection, in relation to the level of lymphopenia (reduced lymphocyte numbers in peripheral blood). These data will be described qualitatively, and do not require statistical analysis.

**Cohort B:** secondary parameters in cohort B are the measurement and characterization of MV-specific humoral and cellular immune responses. Massive expansion of MV-specific (and bystander) B- and T-lymphocyte populations is an essential characteristic of our immune suppression model; we will explore different methods to demonstrate that the qualitative composition of the circulating lymphocyte pool of children after measles is dramatically altered as compared to the pre-infection sample. If successful, these data will be analysed using a similar approach as above: by paired t-test on log-transformed data or by Mann-Whitney U-test if data are not normally distributed.

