**SUMMARY**

**Rationale:** Measles remains an important vaccine-preventable cause of morbidity and mortality. Hallmark of the disease is a transient but severe immune suppression, which results in increased susceptibility to opportunistic infections. In the Netherlands, children are usually vaccinated against measles at the ages of 14 months and 9 years. However, a group of socio-geographically clustered orthodox Protestants refuses vaccination on religious grounds. As a result, outbreaks of infectious diseases are repeatedly observed in this community. The last measles outbreak occurred in 1999/2000, and a new outbreak has started in June 2013.

**Objective:** Using an animal model for measles, we have recently developed a hypothesis to explain the mechanism of measles immune suppression. We hypothesize that MV causes massive infection and subsequent depletion of memory lymphocytes, and thus largely wipes out immunological memory. The objective of the current study is to validate this hypothesis in naturally infected measles patients: we will verify if MV predominantly infects memory lymphocytes, and if this results in depletion of pre-existing memory lymphocytes.

**Study design:** Observational cohort study

**Study population:** Unvaccinated children in orthodox protestant families, 4-17 years of age. This is the only age group eligible for this study, as older children or adults will be immune to measles.

**Intervention (if applicable):** Not applicable

**Main study parameters/endpoints:** The study consists of two cohorts. In cohort A clinical specimens (a blood sample and swabs of the upper respiratory tract) will be collected from children with an acute MV infection, shortly before, at or after onset of rash. The main study parameter in this group will be the characterization of MV-infected lymphocytes in peripheral blood, in order to confirm that the virus predominantly infects memory T- and B-lymphocytes. In cohort B blood samples will be collected from children that have not yet been exposed to MV. A second blood sample will be collected two to three weeks after recovery from measles. The main study parameter in this group will be the quantification of pre-existing memory lymphocyte populations in peripheral blood, to test the hypothesis that these cell populations are decimated during measles.

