### **Cohort A:**

- Measure MV-specific antibody concentrations in the plasma of acute measles patients;
- Measure diagnostic haematological parameters, including numbers (and differentiation) of white blood cells, red blood cells, platelets;
- Measure cytokine, chemokine and acute phase protein concentrations in the plasma of acute measles patients, as correlates of the ongoing MV-specific immune response;
- Assess the shape and size of MV particles directly in throat- and nose swabs and in PBMC, using electron microscopy;
- Determine viral loads in throat- and nose swabs and PBMC of acute MV patients by virus isolation and RT-PCR;
- Determine the difference between cell-free and cell-associated MV in throat- and nose-swabs;

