#### 5.1.2 Secondary study parameters/endpoints (if applicable)

**Cohort A:** secondary study parameters in cohort A are the identification and characterization of cell-free and cell-associated virus, both in terms of quantity (what virus concentrations are present in the upper respiratory tract in relation to transmissibility of MV) and quality (what does transmissible MV look like under the electron microscope?). In addition, we will investigate what cytokines, chemokines and acute phase proteins can be measured in the plasma during the early stage of acute MV infection, in relation to the level of lymphopenia (reduced lymphocyte numbers in peripheral blood).

**Cohort B:** secondary parameters in cohort B are the measurement and characterization of MV-specific humoral and cellular immune responses. Massive expansion of MV-specific (and bystander) B- and T-lymphocyte populations is an essential characteristic of our immune suppression model, so we will investigate whether the quantitative and qualitative composition of the circulating lymphocyte pool of children after measles has indeed changed when compared to the pre-infection sample, while the composition of the paired samples of the control children remains essentially unaltered.

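### Section 6.2 exempts all cohort A secondary data from statistical analysis, although only the electron-microscopy part is qualitative; the stated difference and relation would be reported without uncertainty

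*Protocol*

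**What the plan says.** The protocol's Objectives list measured aims for cohort A. One is "Determine viral loads in throat- and nose swabs and PBMC of acute MV patients by virus isolation and RT-PCR". Another is "Determine the difference between cell-free and cell-associated MV in throat- and nose-swabs". The same list includes plasma concentrations of cytokines, chemokines and acute phase proteins, and white-cell numbers with differentiation.

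Sections 5.1.2 and 6.2 restate the virus endpoint as having a quantity part and a quality part, "both in terms of quantity (what virus concentrations are present in the upper respiratory tract in relation to transmissibility of MV") and the electron-microscopic appearance. They also ask which plasma proteins can be measured, "in relation to the level of lymphopenia (reduced lymphocyte numbers in peripheral blood").

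Section 6.2 then closes the cohort A paragraph: "These data will be described qualitatively, and do not require statistical analysis". In the next paragraph, cohort B's secondary parameters are given a paired test on log-transformed data, with a non-parametric fallback, if the methods explored prove successful.

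On timing, the Summary allows cohort A samples "shortly before, at or after onset of rash". Section 8.1 records days from rash for each cohort A child. Section 6 uses that variable for the infected-cell percentages: "These data will be linked to the time point of sample collection, expressed as the number of days before or after onset of rash". It is not assigned to the secondary parameters.

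**The concern.** A difference between two measured fractions and a relation between two measured variables are quantities to be estimated. A reader needs their size and precision. The closing sentence of the cohort A paragraph suits micrographs and does not suit the rest of what it covers. This is a positive statement in the protocol, not a detail left to a statistical analysis plan. A plan that followed it would contain no analysis of these endpoints, and one that added an analysis would depart from it.

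Two things are at stake. First, the virus contrast and the protein-lymphopenia relation would be reported without intervals, so a reader could not tell an absent relation from a moderate one. Second, lymphocyte counts and plasma proteins may both change over the course of infection. The protocol says measles causes lymphopenia (section 1.4), and the Objectives treat the plasma proteins as markers of the developing immune response. Children sampled at different stages could therefore show a relation that reflects only stage. The variable needed to examine this is recorded but not linked to these endpoints.

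**Working it through.** **No figure to reproduce.** The protocol gives no significance level, power, effect size or standard deviation for these endpoints. The check is therefore a comparison of the text, followed by an illustration under stated assumptions.

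**Step 1: does each endpoint fit the closing sentence of section 6.2?**

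| Cohort A secondary item | Type of result | Fits? |
|---|---|---|
| Virus appearance by electron microscopy | Description | Yes |
| Particle size by electron microscopy | Measured, but descriptive | Largely |
| Viral loads in swabs and PBMC | Number per sample | No |
| Cell-free versus cell-associated virus | Difference | No |
| Plasma proteins in relation to lymphopenia | Association | No |

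Exploratory status does not explain the exemption, because cohort B's secondary parameters are also exploratory and do receive an analysis.

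**Step 2: how imprecise would a correlation be?** The Fisher interval is tanh(atanh(r) ± 1.96/√(n − 3)). The number of children with usable plasma is not stated. Section 1.4 sets 25 successful PBMC stains as the target and 100 children as the maximum, so both are shown, with 50 between them.

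For n = 25, the half-width on the Fisher scale is 1.96/√22 = 0.418. With r = 0.3, atanh(0.3) = 0.310, giving tanh(−0.108) to tanh(0.727), or −0.11 to 0.62.

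| Observed r | n = 25 | n = 50 | n = 100 |
|---|---|---|---|
| 0 | −0.40 to 0.40 | −0.28 to 0.28 | −0.20 to 0.20 |
| 0.3 | −0.11 to 0.62 | 0.02 to 0.53 | 0.11 to 0.47 |
| 0.5 | 0.13 to 0.75 | 0.26 to 0.68 | 0.34 to 0.63 |

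Estimation is possible but imprecise, which is the reason to print the interval.

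**Step 3: what could a shared time course do?** Suppose a plasma marker and the lymphocyte measure each correlate ρ with time from rash, linearly and in the same direction, and are otherwise unrelated. The expected crude correlation is then ρ × ρ: 0.3² = 0.09, 0.5² = 0.25, 0.7² = 0.49. Opposite directions would change only the sign. A simulation of 5,000 trials per setting shows how often a crude correlation would reach two-sided p < 0.05:

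| ρ with time (assumed) | Expected crude r | n = 25 | n = 50 | n = 100 |
|---|---|---|---|---|
| 0.3 | 0.09 | 6% | 9% | 14% |
| 0.5 | 0.25 | 23% | 40% | 70% |
| 0.7 | 0.49 | 73% | 96% | 100% |

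With the partial correlation given time, the rate is 4% to 6% in every setting. The protocol plans no such test. The percentages only gauge how readily a pattern due to time alone could look convincing. The values of ρ are assumptions, and the protocol offers nothing to narrow them.

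**The case against.** The strongest defence is that these are secondary, exploratory endpoints with no hypothesis attached, and that description without inference is a legitimate choice. Several parts of it stand.

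- **The wording is not a prohibition.** A reader might infer that section 6.2 forbids statistical analysis and that the two questions cannot be answered. The text does not support this. It says analysis is not required. Medians, paired plots and scatter plots would answer both questions descriptively. What they would lack is uncertainty.
- **The protocol uses the word qualitative loosely.** Section 6 states "In cohort A the outcomes will be presented as qualitative data: the percentage MV-infected cells" and then tests those percentages. Numerical summaries of the secondary data are therefore not excluded. This softens the first half of the sentence in section 6.2, but not the second half, which says that statistical analysis is unnecessary.
- **A false relation is not demonstrated.** A reader might infer from step 3 that the trial will report a spurious finding. The rates concern a test that the plan does not run. With the weakest time effect shown, the rate at n = 25 is 6%, close to nominal. The Study Design section also aims for samples before rash, and a narrower spread of sampling times would weaken the effect.
- **The number 25 is not the sample size here.** It is the PBMC-stain target. Swabs and plasma may be available from more children.
- **Pairing is not stated.** The Objectives ask for a difference in throat and nose swabs and do not say that both fractions come from one swab. Section 1.4 accepts that uninfected children may be enrolled, and virus may be undetectable in some samples. A simple mean log difference may therefore not be computable for every child.
- **Adjusting for time is a choice of estimand.** If disease stage is part of the question, the crude relation is also of interest.

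What does not stand is the claim that exploratory status settles the matter. The adjacent cohort B paragraph is equally exploratory and has an analysis.

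**Conclusion.** The point holds in a limited form. The closing sentence of the cohort A paragraph in section 6.2 covers viral loads, a difference and a relation, and it suits only the electron-microscopy description. Followed as written, the trial would report the difference and the relation without a measure of uncertainty. At n = 25, an observed correlation of 0 is compatible with anything from about −0.40 to 0.40; at n = 100, with −0.20 to 0.20.

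Confounding by time from rash is a reasonable inference from the sampling window, but its size is unknown. The illustration ranges from negligible to severe depending on the assumed link with time, and it assumes linear trends. The primary analyses of both cohorts are untouched. Priority is low.

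**What to change.** In section 6.2:

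1. Limit the statement about qualitative description to the electron-microscopy data.
2. For laboratory-confirmed cases, report the within-child contrast of cell-associated with cell-free virus quantity on the log scale, with a 95% confidence interval. State whether the two fractions come from the same swab. Use a paired rank-based or a censored-data method where virus is undetectable.
3. Report each plasma marker's rank correlation with lymphocyte count, with a 95% confidence interval, both crude and adjusted for (or displayed by) days from rash.
4. Label all of these exploratory.

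Days from rash are already recorded, and lymphocyte numbers and plasma proteins are already to be measured. No further children, blood or swabs are needed. The cost is a few sentences and a little more analysis work. The drawback is that the intervals will be wide.
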